## Abstract

**Background:**

Noninvasive ventilation (NIV) is indicated to treat respiratory acidosis due to exacerbation of chronic obstructive pulmonary disease (COPD). Recent nonrandomized studies also demonstrated some physiological effects of high-flow nasal therapy (HFNT) in COPD patients. We designed a prospective, unblinded, multicenter, randomized controlled trial to assess the noninferiority of HFNT compared to NIV with respect to the reduction of arterial partial pressure of carbon dioxide (PaCO_2_) in patients with hypercapnic acute respiratory failure with mild-to-moderate respiratory acidosis.

**Methods:**

We will enroll adult patients with acute hypercapnic respiratory failure, as defined by arterial pH between 7.25 and 7.35 and PaCO_2_ ≥ 55 mmHg. Patients will be randomly assigned 1:1 to receive NIV or HFNT. NIV will be applied through a mask with a dedicated ventilator in pressure support mode. Positive end-expiratory pressure will be set at 3–5 cmH_2_O with inspiratory support to obtain a tidal volume between 6 and 8 ml/kg of ideal body weight. HFNT will be initially set at a temperature of 37 °C and a flow of 60 L/min. At 2 and 6 h we will assess arterial blood gases, vital parameters, respiratory rate, treatment intolerance and failure, need for endotracheal intubation, time spent under mechanical ventilation (both invasive and NIV), intensive care unit and hospital length of stay, and hospital mortality.

Based on an α error of 5% and a β error of 80%, with a standard deviation for PaCO_2_ equal to 15 mmHg and a noninferiority limit of 10 mmHg, we computed a sample size of 56 patients. Considering potential drop-outs and nonparametric analysis, the final computed sample size was 80 patients (40 per group).

**Discussion:**

HFNT is more comfortable than NIV in COPD patients recovering from an episode of exacerbation. If HFNT would not be inferior to NIV, HFNT could be considered as an alternative to NIV to treat COPD patients with mild-to-moderate respiratory acidosis.

**Trial registration:**

ClinicalTrials.gov, NCT03370666. Registered on December 12, 2017.

**Electronic supplementary material:**

The online version of this article (10.1186/s13063-019-3514-1) contains supplementary material, which is available to authorized users.

## Background

Severe exacerbation of chronic obstructive pulmonary disease (COPD) is defined as an acute worsening of chronic respiratory symptoms and decompensated respiratory acidosis [1]. In the case of hypercapnic acute respiratory failure (ARF), the sole optimization of standard medical therapy may fail in up to 74% of patients [2]. In addition to pharmacological therapy, recent guidelines recommend the use of noninvasive ventilation (NIV) in the absence of metabolic causes of acidosis [1, 3]. Indeed, NIV improves vital signs and gas exchanges [2, 4], increasing alveolar ventilation [5]. NIV also reduces the patient’s effort [6], dyspnea [2, 7], the need for intubation [2, 8, 9], the intensive care unit (ICU) length of stay [9] and the mortality rate [2, 9, 10]. However, there are several determinants for NIV success, including comfort related to the interface and patient–ventilator interaction [4, 11–18].

High-flow nasal therapy (HFNT) is a more recent treatment, which delivers a heated and humidified air–oxygen mixture at high flow (up to 60 L/min) through large-bore nasal cannula [19, 20]. Compared to standard oxygen therapy, HFNT washes out the anatomical dead space of the upper airway, generates a certain amount of expiratory pharyngeal pressure proportional to the flow, which increases the end-expiratory lung volume, slows the respiratory rate by decreasing the respiratory time [21], promotes the clearance of tracheobronchial secretions and reduces the inspiratory effort [22–24].

While a large body of evidence is already supporting the use of HFNT in critically ill patients with hypoxemic ARF [23, 25–28], few studies have evaluated its effectiveness in COPD patients [20]. In stable COPD patients, HFNT reduces the respiratory rate [29] and the arterial partial pressure of carbon dioxide (PaCO_2_) [29, 30], increases the tidal volume and the end-expiratory lung volume [29], and reduces the work of breathing and the rapid shallow breathing pattern [31, 32]. In patients recovering from an episode of hypercapnic ARF due to COPD exacerbation, the respiratory rate and drive significantly increase with standard oxygen at NIV discontinuation, while not with HFNT [33]. Furthermore, HFNT guaranteed optimal comfort [22, 34].

A recent prospective observational trial enrolling 92 patients with severe COPD exacerbation and moderate hypercapnic acute respiratory failure found no difference in 30-day mortality and the intubation rate between HNFT and NIV [34]. Currently, no randomized controlled trials have compared the efficacy of HFNT with that of NIV as first-line treatment in exacerbated COPD patients.

We conceived the present protocol in order to evaluate whether HFNT is noninferior to NIV in reducing PaCO_2_, in patients with an exacerbation of COPD and mild-to-moderate respiratory acidosis.

## Methods

### Study design

This is an investigator-initiated, unblinded, multicenter, noninferiority, randomized controlled trial. Randomization has been achieved using a computer-generated randomization sequence, generated by an independent investigator not otherwise involved in the trial, with an allocation ratio of 1:1 and with a permuted block method. A single randomization list was created for all participants. Allocation concealment has been maintained by using sequentially numbered sealed opaque envelopes. Each envelope contains the allocation of the patient to either control (NIV) or intervention (HFNT), with a unique patient identifier code. The randomization is based on a centralized phone call system. Due to the research design, neither the individual collecting data nor the patient can be blinded to treatment allocation.

The study was prospectively registered with ClinicalTrials.gov in December 2017 (identifier: NCT03370666). This protocol has been designed in accordance with the Standardized Protocol Items: Recommendations for Interventional Trials (SPIRIT) guidelines and checklist (Additional file 1). A schedule for enrolment, intervention and assessment (SPIRIT figure) is outlined in Fig. 1. A CONsolidated Standards of Reporting Trials (CONSORT) diagram is shown in Fig. 2.

**Fig. 1 Fig1:**
[figure not shown]
A schedule for enrolment, intervention and assessment according to the Standard Protocol Items: Recommendations for Interventional Trials (SPIRIT) indications. HFNT high-flow nasal therapy through nasal cannula, ICU intensive care unit, NIV noninvasive ventilation

**Fig. 2 Fig2:**
[figure not shown]
Study flow chart according to CONsolidated Standards of Reporting Trials. COPD chronic obstructive pulmonary disease, HFNT high-flow nasal therapy through nasal cannula, ICU intensive care unit, NIV noninvasive ventilation, PaCO_2_ arterial partial pressure of carbon dioxide

### Study population

We will consider eligible consecutive adult (i.e. ≥ 18 years/old) patients with a diagnosis of COPD according to the GOLD criteria [1] admitted for an acute-on-chronic respiratory failure due to exacerbation, with arterial pH between 7.25 and 7.35 and PaCO_2_ ≥ 55 mmHg, to the emergency department or ICU or respiratory unit of the participating centers. Written informed consent will be acquired before the patient’s inclusion. Patients will be excluded if they meet one or more of the following criteria: already received HFNT or NIV, prior to study enrolment; long-term domiciliary NIV; clinical instability, as defined by the need for vasopressors, acute coronary syndrome or life-threatening arrhythmias [35]; treatment refusal; agitation, as defined by Richmond Agitation Sedation Scale (RASS) score ≥ 2, or lack of collaboration, as defined by Kelly Matthay score ≥ 5 [35]; acute failure of more than two organs [35]; cardiac arrest; respiratory arrest deeming immediate intubation; recent trauma or bursts on the neck or face; pregnancy; consent withdrawal; and enrolment in other research protocols. The study flow chart is shown in Fig. 2.

### Intervention group

Patients randomized to the intervention group will receive HFNT (Optiflow and MR850 or AIrVO_2_™; Fisher & Paykel Healthcare, Auckland, New Zealand), initially set at 60 L/min and a temperature of 37 °C. In the case of discomfort, the flow and/or temperature will be downregulated to the most tolerated setting. In the HFNT group, a rescue NIV treatment will be allowed in the case of worsening of respiratory failure and/or treatment failure, before proceeding with an eventual endotracheal intubation and invasive mechanical ventilation.

### Control group

Patients randomized to the control group will receive NIV applied through a total full-face or oro-nasal mask. The ventilator will be set in pressure support ventilation (PSV) mode, with positive end-expiratory pressure (PEEP) between 3 and 5 cmH_2_O. The inspiratory pressure support will be regulated in order to achieve a measured or estimated tidal volume equal to 6–8 ml/kg of ideal body weight [35]. The treating physicians, based on local availability, will choose the ventilators used to deliver NIV.

In both groups, treatment other than ventilatory support will be supplied according to current guidelines [1]. Sedatives will be allowed to improve the patient’s comfort and tolerance of the interfaces. The inspired oxygen fraction (FiO_2_) will be set to maintain a peripheral saturation (SpO_2_) target between 88 and 92% [1]. In the case of treatment interruption due to any reason, patients will receive oxygen supply through a Venturi mask to achieve the same SpO_2_ target. During study interventions, patients will be monitored by at least continuous SpO_2_, electrocardiogram and noninvasive blood pressure.

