### Study endpoints

The primary endpoint of the study will be to evaluate whether HFNT is noninferior to NIV in reducing PaCO_2_, at 2 h after the group allocation, in patients with exacerbation of COPD and mild-to-moderate respiratory acidosis. The secondary endpoints will be: noninferiority of HFNT to NIV in reducing PaCO_2_ at 6 h after randomization; dyspnea score; treatment failure rate; discomfort related to the interface or to symptoms related to airway and mouth dryness; respiratory rate; need for endotracheal intubation; time spent under mechanical ventilation (both invasive and NIV); ICU and hospital length of stay; and hospital mortality.

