### Data collection and outcome assessment

For each patient, we will collect anthropometric data (age, gender, weight and height) and baseline characteristics (the Simplified Acute Physiology Score (SAPS II), the Kelly-Matthay score [36], the Charlson index [37] and the Richmond Agitation Sedation Scale (RASS) score [38]). Furthermore, soon before randomization we will record vital parameters (heart rate, blood pressure, breath frequency and temperature), the amount of secretions, the presence of dyspnea (as reported by the patient through the Borg scale) [39] and arterial blood gases (ABGs) at patient inclusion.

At 2 and 6 h after the patient’s randomization to receive NIV or HFNT, we will collect all vital parameters, ABGs, the RASS score, the Kelly-Matthay score [36], the grade of dyspnea and the need for sedatives. Sedation will be allowed to increase tolerance to the treatment [40, 41]. Moreover, we will record: the settings of NIV and HFNT; the discomfort related to the interface, as assessed through a 11-point Numeric Rating Scale (NRS) [15, 42, 43]; and the intolerance to the interface due to flow, temperature, noise, claustrophobia, sweating, tightness, airway dryness, vomiting gastric distension, ocular irritation or skin breakdown, separately [42, 44, 45].

We will also record: the rate of treatment intolerance, as defined by the inability of the patient in continuing NIV or HFNT treatment; the rate of treatment failure, as defined by the presence of PaCO_2_ worsening or reduction < 10 mmHg from baseline assessment, or worsening or no improvement of dyspnea, or respiratory rate > 30 breaths/min; need for endotracheal intubation; time spent under mechanical ventilation (both invasive and NIV); ICU and hospital length of stay; and hospital mortality.

The decision to intubate the patient will be taken by the physician in charge of the patient, in the case of the presence of one of the following criteria: respiratory arrest, respiratory apnea or pauses with loss of consciousness, severe agitation, bradycardia (< 50 beats/min) with loss of consciousness, hemodynamic instability with systolic arterial pressure < 70 mmHg, need for invasive mechanical ventilation due to worsening in arterial blood gases and pH, need for suctioning due to unmanageable secretions or intolerance to all of the interfaces (including shift of treatment to NIV in the HFNT group).

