### Statistical analysis

For the purpose of the study, we computed a sample size of 56 patients, given an α error of 5% (one-sided) and a β error of 80%, with a standard deviation for the primary outcome equal to 15 mmHg and a noninferiority limit of 10 mmHg [35]. After considering potential drop-outs (30%) [35] and an increase in sample size for nonparametric analysis (15%), the final computed sample size was 80 patients (40 per group).

An independent investigator, blinded to treatment allocation, will undertake all statistical analyses on an intention-to-treat basis. After checking the Gaussian distribution, continuous data will be presented as mean (standard deviation) or median (25th–75th IQR).

Categorical data will be expressed as count and percentage. Continuous data will be compared by the Mann–Whitney *U* test or the Student *t* test, and categorical data by the chi-square test or the Fisher exact test [46]. The Kruskal–Wallis test will be used to check between-group differences at baseline, 2 h and 6 h. Friedman’s test or repeated-measures ANOVA will be used to check within-group differences at different time points. *p* < 0.05 will be considered significant.

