## Discussion

HFNT is increasingly used in different settings [23, 25–27]. Some studies indicate that HFNT has physiological advantages in both stable and exacerbated COPD patients [20]; in particular, in patients recovering from an episode of hypercapnic ARF due to COPD exacerbation, HFNT reduces the respiratory effort and rate no differently from NIV, while it maintains similar gas exchanges and improved comfort [22]. A recent observational trial found no difference between NIV and HNFT in terms of 30-day mortality and intubation rate in severe exacerbation of COPD [34].

Currently, NIV is strongly suggested as standard treatment for exacerbated COPD patients with respiratory acidosis [3]. However, NIV is affected by several drawbacks such as reduced comfort and poor patient–ventilator interaction and synchrony, which is often difficult to be recognized and managed [4, 11–13, 16]. We therefore design this randomized controlled trial to assess the noninferiority of HFNT in reducing the PaCO_2_, as compared to NIV. In fact, whenever the trial demonstrates a noninferiority of HFNT compared to NIV, the physician may use HFNT as an alternative ventilatory support in exacerbated COPD patients with mild-to-moderate respiratory acidosis. This would also allow the possibility to use another support with a different interface in a rotational strategy to improve the patient’s comfort and tolerance to the treatment [47, 48]. This trial has limitations. First, blinding is not possible due to the nature of the interventions. Second, although recruitment centers have established experience in the use of ventilator support in this patient population, different practices in the use of both NIV and HNFT may influence the effect of the interventions. However, recruitment centers have established experience in the use of ventilator support in this patient population. Third, the study is a noninferiority trial with a physiologic outcome, leaving uncertainty on stronger patient-related outcomes. It is anticipated that the results of this study will be used to design further randomized clinical trials powered to assess major clinical outcomes.

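### PaCO2 drawn while the allocated device is interrupted counts as that arm's result under an intention-to-treat-only analysis, which can favour noninferiority; the device in use at each gas should be recorded and a supportive on-device analysis added

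*Protocol article*

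**What the plan says.** Four statements in the Protocol article bear on this.

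- **Timing of the primary endpoint (Study endpoints).** PaCO2 is compared "at 2 h after the group allocation". The 6 h comparison, a secondary noninferiority endpoint, is also counted from randomization.
- **Timing of the samples (Data collection and outcome assessment).** At 2 and 6 h after "randomization to receive NIV or HFNT, we will collect all vital parameters, ABGs" and other items. Device settings are recorded as well. The article gives no condition on what the patient is breathing through when the sample is drawn.
- **Interruptions (Control group, the paragraph that applies to both arms).** "In the case of treatment interruption due to any reason, patients will receive oxygen supply through a Venturi mask", aiming at the same saturation target.
- **Analysis (Statistical analysis).** Every analysis follows intention to treat. No other analysis set is named.

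On tolerability, the Discussion states that "NIV is affected by several drawbacks such as reduced comfort", and the Abstract describes HFNT as the more comfortable of the two in patients recovering from an exacerbation. Neither place gives an interruption rate.

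**The concern.** The trial asks whether HFNT lowers PaCO2 no worse than NIV by more than 10 mmHg. A gas that falls due while the mask is off reflects Venturi oxygen, yet it enters the NIV mean. If NIV works better than Venturi oxygen, such values raise the control mean and bring the arms closer together. In a superiority trial that would cost power. In a noninferiority trial it raises the chance of a false positive claim on the primary endpoint, and again at 6 h. With intention to treat as the only stated analysis, nothing in the article would show a reader whether this had happened.

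This is separate from rescue NIV in the HFNT arm. Rescue moves HFNT patients onto the comparator; an interruption moves patients in either arm onto plain oxygen.

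**Working it through.** **Inputs from the article.** Error rates: "given an α error of 5% (one-sided) and a β error of 80"% (the second figure is read as 80% power). Variability and margin: "with a standard deviation for the primary outcome equal to 15 mmHg and a noninferiority limit of 10 mmHg". Allocation: "with an allocation ratio of 1:1 and with a permuted block method". Size: "we computed a sample size of 56 patients", raised to 80 (40 per group), with a 30% drop-out allowance.

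**Reproducing the plan's figure.** Assume a true difference of 0, which the article does not state. Then n per arm = 2 × 15² × (1.645 + 0.842)² / 10² = 27.8, rounded up to 28, or 56 in total. This agrees with the article. Forty per arm less 30% is also 28, so 28 and 40 bracket the evaluable number per arm.

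**Rule for claiming noninferiority.** SE = 15 × √(2/n), and noninferiority is claimed if the observed difference (HFNT minus NIV) is below 10 − 1.645 × SE.

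- n = 28: SE = 4.009, threshold 3.41 mmHg.
- n = 40: SE = 3.354, threshold 4.48 mmHg.

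**Effect of a shift.** Suppose HFNT is truly 10 mmHg worse on device and off-device gases shrink the observed difference by s. The false-claim rate is Φ(s/SE − 1.645).

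**Assumed s.** The article gives neither the share of gases drawn off NIV nor the PaCO2 penalty. Assume 10–30% off NIV, a penalty of 5–10 mmHg and no HFNT interruptions. Then s runs from 0.10 × 5 = 0.5 to 0.30 × 10 = 3 mmHg.

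| s (mmHg) | 28 per arm | 40 per arm |
|---|---|---|
| 0 | 5.0% | 5.0% |
| 0.5 | 6.4% | 6.7% |
| 1 | 8.1% | 8.9% |
| 2 | 12.6% | 14.7% |
| 3 | 18.5% | 22.6% |

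**Allowing HFNT interruptions.** Let f and g be the shares of NIV and HFNT patients off device. The result depends on what each arm loses.

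1. *Same loss r in both arms.* Observed difference = 10 − f·r + g·r. With f = g it stays at 10 and the rate stays at 5%. With f = 10%, g = 30% and r = 10 it becomes 12, and the rate falls to 1.6% (28 per arm) or 1.3% (40 per arm), so the bias has reversed.
2. *Both arms fall to a common Venturi level, v mmHg above the NIV level.* Observed difference = (1 − g) × 10 + g·v − f·v. With f = g this is 10 × (1 − f), whatever v is. Equal shares of 10, 20 and 30% therefore give s = 1, 2 and 3, the last three rows of the table. The direction reverses only if g/f > v/(v − 10): more than 3 at v = 15, and never at v = 10.

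Under the second model NIV patients have more to lose, so equal interruption is enough to favour noninferiority. Under the first it is not.

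**The case against.** Four objections carry weight.

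- **A condensed article.** A rule that gases be drawn on the allocated device, or a case report form field for it, may sit in the full protocol. That possibility stands, so the point is about what can happen under the stated rules. What the article does state is the clock timing, the Venturi rule and intention to treat as the basis for all analyses.
- **Both arms are covered.** A reader might infer that the Venturi rule weakens only the control arm and that the bias must favour HFNT. The documents do not support this. The rule applies to both groups, and the comfort statements are not interruption rates. The eligibility criteria exclude agitated and uncooperative patients, and sedation is allowed to improve tolerance; both should limit early interruptions.
- **Interruptions are a contingency.** A reader might also infer that the protocol schedules mask breaks, so that a per-protocol set would keep these gases. It schedules none, and it defines no per-protocol set. Nor is exposure wholly unrecorded: settings, inability to continue treatment and total ventilation time are collected. As described, though, none of these shows which device was in use at the 2 h gas or how long it had been used by then.
- **Fixed-time intention to treat is legitimate.** It compares the strategies as delivered, tolerability included. This stands, and it is why the primary analysis should not change. Delaying a gas until the device is resumed would make timing depend on the arm. Restricting to on-device gases selects tolerant patients. The restricted analysis can therefore only be supportive.

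**Conclusion.** The point holds in a conditional form. Under the stated rules, a PaCO2 drawn off the allocated device counts as that arm's result, and the only stated analysis cannot show how often this occurs. If NIV is truly better and is interrupted at least as often as HFNT, the observed difference can shrink and noninferiority becomes easier to claim. With equal interruption, that further requires NIV patients to lose more PaCO2 benefit off device than HFNT patients do.

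The size is unknown. The increase from 5% to 6.4–18.5% (28 per arm) or 6.7–22.6% (40 per arm) rests on an assumed 0.5–3 mmHg net shift with no HFNT interruptions. It should not be read as an estimate for this trial. Equal interruption with equal loss leaves the rate at 5%, and more frequent HFNT interruption could make the comparison conservative. The case for acting is that the possible error is anti-conservative on the primary endpoint and costs little to detect.

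**What to change.** Keep the 2 h and 6 h clock times, the intention-to-treat primary analysis and the rules on interrupting treatment as they are.

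1. **Data collection and outcome assessment:** at each gas, record the device in use and the minutes on the allocated device since randomization. If the full protocol already requires this, confirming it settles this item.
2. **Statistical analysis:** add a supportive noninferiority comparison, with the same margin and one-sided 5% level, restricted to gases drawn on the allocated device. Report it with the intention-to-treat result, together with the number off device in each arm. Require the two to be consistent before noninferiority is claimed, and define consistency in advance.

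**Cost.** Two case report form fields and one further analysis. The restricted analysis conditions on a post-randomization event, so it cannot replace intention to treat. It also has less power. For example, with 28 evaluable per arm and 30% of NIV gases off device (28 × 0.7 ≈ 20 left), SE = 15 × √(1/20 + 1/28) = 4.39, and power at a true difference of 0 is Φ(10/4.39 − 1.645), about 74% against 80% for the full set. The definition of consistency should allow for this.
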